## Abstract

**Background:**

Driving performance involves multiple underlying components of psychomotor functioning, such as attention, executive functions, and vehicle control. While the effects of acute medical marijuana and prescription opioid intoxication are known, how long-term use of medical marijuana under real-world conditions affects driving performance is unknown. Additionally, there are numerous ongoing physical and cognitive changes that affect driving performance with age. Given the proliferation of medical marijuana and prescription opioid use in adults aged 50 years and older, the prevalence of polypharmacy, and declining functional abilities, it is imperative to understand the long-term effects of daily medical marijuana use. Further, we need to understand how co-occurring use of medical marijuana and prescription opioids, in the presence of comorbidities such as chronic pain, affects real-world driving outcomes.

**Objective:**

This study aims to document the observational trial protocol. The primary goal of this study is to identify the effects of daily long-term (ie, use for >12 months daily or most days of the week) medical marijuana use on driving performance outcomes using an open-road driving performance task under real-world conditions in adults aged 50 years and older who endorse chronic or severe nonmalignant pain and to examine the combined effect of daily long-term medical marijuana use and prescription opioid use on driving outcomes. A secondary goal is to qualitatively explore self-regulation of medical marijuana and prescription opioid use in this population.

**Methods:**

We plan to test medical marijuana use as the exposure variable in adults aged 50 years and older on an open-road driving task performance as the primary outcome. The study will detail tetrahydrocannabinol exposure through ecological momentary assessment and urinalysis and will compare performance with a race-sex–matched group of non–marijuana users.

**Results:**

This study is funded by a grant from the National Institute on Drug Abuse (5R01DA057965). Recruitment began on May 19, 2025. As of November 2025, a total of 30 participants had been enrolled. Recruitment is anticipated to be completed by 2029. Publication of the complete results and data from this study is expected by 2030.

**Conclusions:**

Data from this study will identify the effects of long-term medical marijuana use and the combined effect of that use with prescription opioids to develop risk screening protocols and intervention targets for this population. The development and dissemination of screening and intervention guidelines will be the next step in this work.

**Trial Registration:**

ClinicalTrials.gov NCT06995937; https://www.clinicaltrials.gov/study/NCT06995937

**International Registered Report Identifier (IRRID):**

DERR1-10.2196/77944

## Introduction

With increasing marijuana use, cannabinoids have become one of the most frequently encountered psychoactive substances in the blood or oral fluids of drivers who are drug-impaired or involved in motor vehicle accidents [1]. The 2015 US National Roadside Survey showed that the rate of tetrahydrocannabinol (THC)–positive drivers increased 48% among all drivers [2]. Further, THC is associated with a 50% increased risk for traffic crashes [3,4], and the risk of motor vehicle collision while driving under the influence of marijuana is twice as high as when driving unimpaired [1,5]. Opioid use is associated with a 47% increased risk of crash involvement [6,7]. Further, motor vehicle collisions are among the leading causes of unintentional morbidity and mortality in North America [8,9]. While the cause of motor vehicle collisions is multifaceted, a potential contributor is the use of psychoactive medications such as prescription opioids [6,10,11]. Due to developmental life stage, older adults have a higher risk for multiple drug use, including polypharmacy [12], which puts them at a higher risk for drug-drug interactions [13]. Driving performance involves multiple underlying components of psychomotor functioning, such as attention, executive functions, and vehicle control [14]. While the effects of acute medical marijuana and prescription opioid intoxication are known [13,15-17], how long-term use of medical marijuana affects driving performance—a complex skill needed for continued independence with age—is unknown. Additionally, there are numerous ongoing physical and cognitive changes that affect driving performance with age [18,19]. Given the proliferation of medical marijuana use and prescription opioid use in adults aged 50 years and older [20-23], the prevalence of polypharmacy, and declining functional abilities, it is imperative that we understand the long-term effects of daily medical marijuana use. Further, we need to understand how co-occurring use of medical marijuana and prescription opioids, in the presence of comorbidities such as chronic pain, affects real-world driving outcomes.

Findings regarding the effects of long-term marijuana use are mixed. Some evidence indicates that long-term, heavy cannabis use (ie, daily or almost daily use) may cause impairment in cognitive and motor functions [24]. Long-term heavy use is associated with decreased motor control, decreased attentional control in both sustained and divided attention, greater cognitive impairment, and greater short-term memory deficits [24,25]. Current heavy use is also associated with decreased vehicle control [1]. However, some studies suggest that impairment due to long-term heavy use does not persist after extended abstinence periods and that mild to moderate use is not associated with impairment [26].

For mid- to late-life adults, participation in driving activities allows them to meet their social roles and stay independent [14,27,28]. Factors such as age-related functional impairments due to chronic pain and side effects of medications such as medical marijuana and prescription opioids can compromise participation in driving and lead to heightened crash risk [28-30]. In the United States in 2015, more than 85% of adults aged 65 to 84 years and nearly 70% of adults aged 85 years and older were licensed to drive [31]. By 2030, the number of older adults is projected to account for 21% of the US population, and most older adults will retain their driver’s licenses [32,33].

To date, no studies have systematically assessed driving performance in a rigorous and ecologically valid manner accounting for long-term medical marijuana use and the combined effect of prescription opioid use in adults aged 50 years and older, who endorse chronic or severe nonmalignant pain. Further, studies examining how older adults self-regulate prescription medication use and driving behavior are limited, with none rigorously examining medical marijuana.

Thus, the overall objective of this study is to address the research questions: Does daily long-term medical marijuana use affect performance on an open-road driving task in adults aged 50 years and older who endorse chronic or severe nonmalignant pain, and what is the combined effect of long-term medical marijuana and prescription opioid use on driving performance outcomes in this population?

## Methods

### Ethical Considerations

This research was approved by the Florida State University Institutional Review Board (STUDY00005560) in December 2024. Informed consent is obtained prior to beginning any study procedures. Participation is completely voluntary. Participant privacy and data confidentiality are protected through multiple measures, including a private interview setting for all study procedures, a Health Insurance Portability and Accountability Act (HIPAA)–compliant data storage platform (Research Electronic Data Capture [REDCap; Vanderbilt University]) and text message delivery application (Mosio), and coding of all data so that it cannot be associated with any individual. Participants will receive up to US $245 if all assessments are completed as directed in the study protocol.

### Study Design

We are using a two-group observational study design with a group with medical marijuana use for more than 12 months daily or most days of the week (medical marijuana group [MMG]) versus a race-sex–matched group with no marijuana exposure in the past 10 years and no history of daily use (no marijuana group [NMG]). We chose 10 years as the no–marijuana-exposure window to ensure that recreational use was not a confounder. We will test the difference between long-term medical marijuana exposure and no marijuana exposure on driving performance outcomes in adults aged 50 years and older who endorse chronic or severe nonmalignant pain through an open-road driving assessment. There will be up to 3 in-person assessment sessions over approximately 10 days. Assessment session 1 (AS1; the first assessment session) is the onboarding session, which will include informed consent, sociodemographics, a battery of psychosocial measures, and urinalysis to test for the presence of marijuana, opioids, and other commonly misused substances. After AS1, we will use ecological momentary assessment to capture medical marijuana use (MMG) or mood and medication use (NMG). MMG participants will complete twice-daily assessments of medical marijuana use for 7 days. To attention match, the NMG will complete twice-daily assessments of mood and any medication use daily for 7 days. Assessment session 2 (AS2; the second assessment session), the open-road driving performance task, will occur approximately 8 days after AS1 and, for MMG participants, 8-12 hours after the last medical marijuana use. At AS2, vision screening to ensure appropriate visual acuity and urinalysis will be completed before the drive. Additionally, we will request permission from MMG participants only to extract Office of Medical Marijuana Use (OMMU) purchase history data, which include the dispensary name, date of purchase, quantity of medical marijuana purchased, and route of administration. Assessment session 3 (AS3; the third and final assessment session) will be a qualitative interview with a subset of participants (n=60) regarding self-regulation of medical marijuana and prescription medication use, to be completed no later than 3 days after the drive (Figure 1).

**Figure 1 figure1:**
[figure not shown]
Study flowchart. LC/MS-MS: liquid chromatography–tandem mass spectrometry; MMTC: Medical Marijuana Treatment Clinics of Florida.

This study is designed to address an urgent public health issue: “What are the effects of chronic, habitual marijuana use on adults aged 50 years and older?” Mid- to late life is a sensitive time period that involves significant changes that can impact quality of life, and understanding how chronic habitual marijuana use affects cognitive and psychomotor function is a significant and vital public health question. This study is designed to obtain data needed for the development of guidelines and best practices for use among adults aged 50 years and older who use marijuana daily or most days. The primary outcome, driving performance, is a vital measure of continued independence with aging and represents a real-world activity that captures cognitive, motor, memory, and executive functions in a single task. Therefore, the estimand of this study is to understand the difference in driving performance errors (ie, lane maintenance errors, speed regulation errors, adjustment-to-stimuli errors, yielding errors, signaling errors, vehicle positioning errors, visual scanning errors, and gap acceptance errors) among adults aged 50 years and older who have used medical marijuana daily or most days for at least the past year (MMG), as compared race-sex–matched adults who do not consume any marijuana (NMG). Further, we are intentionally using an 8- to 12-hour timeframe, as that is consistent with how adults in this population report marijuana consumption behavior in relationship to driving. This study design maximizes both ecological and external validity by estimating group differences in performance that reflect long-term neuroadaptation and real-world use patterns rather than acute intoxication. In addition, urine metabolites are collected before each drive so chronicity of marijuana use will be on a continuous spectrum as measured by 11-nor-9-carboxy-tetrahydrocannabinol (THC-COOH) output. The focus of our study design is to better understand chronic habitual use and whether there are any impacts on driving performance under real-world conditions.

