#### Assessment Session 2 (Driving Performance Task)

Participants will arrive at the UF Smart House either by Uber or by a driver of their choice. For MMG participants only, AS2 will take place 8-12 hours after the last medical marijuana use. Upon arrival at the Smart House, a study team member will complete vision screening with the UFOV (Posit Science) and Optec 5000 (Stereo Optical) visual analyzer machine and collect a urine sample for urinalysis. A portion of the urine provided by MMG participants will be reserved for analysis using liquid chromatography–tandem mass spectrometry, which provides a more precise measurement of the level of THC-COOH, a metabolite of THC, present in urine. We will request permission from MMG participants only to extract OMMU purchase history data, which includes the dispensary name, date of purchase, quantity of medical marijuana purchased, and route of administration.

The CDRS or DRT will begin the open-road driving performance task evaluation, which begins with a standardized field sobriety test to detect the presence or absence of horizontal gaze nystagmus, the involuntary jerking or sudden eye movement that naturally occurs when the eyes gaze to the side [39]. The evaluator will instruct participants to focus on and follow the trajectory of a slow-moving horizontal object, typically a pen, presented directly in front of their face. The evaluator will observe both the right and left eye for 3 distinct signs: lack of smooth pursuit, distinct nystagmus at the maximum eye deviation (N_max_), and onset of nystagmus prior 45° deviation (N45) [40]. These signs will be recorded as “present” or “absent,” and participants will be classified as “failed” if all factors are noted as “present.” Participants who fail the sobriety test will be informed that they cannot complete the drive and will be compensated US $20 for a partial AS2 visit.

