## Discussion

### Expected Findings

Our work will (1) focus on medical marijuana use with a sample who has used daily or most days for 12 months or longer, (2) confirm medical marijuana use based on date of card qualification and purchase history—all products used in the previous year will be downloaded from the OMMU to quantify use patterns over the course of the past year, (3) quantify medical marijuana use for 7 days before the on-road driving performance task using twice-daily ecological momentary assessment for all MMG participants, (4) measure prescription opioid using urinalysis on the day of the drive, and (5) measure driving performance using an open-road course under the observation of a CDRS or DRT trained to evaluate impaired driving in a test vehicle with the needed evaluator controls (eg, eye check mirrors and auxiliary brake) to maneuver the car and prevent any adverse occurrences, including near misses or crashes, if any dangerous situations arise. Older adults are more likely to be involved in crashes at intersections or during merges, and these crashes are inherently more fatal [45,46]. The challenging, fast-paced environment presented by intersections and merges puts extra demand on cognitive, sensory, and motor domains critical for driving, and slower response time, inattention, and difficulty with executive functions may lead to more driving errors, potential crashes, or fatal crashes [44]. Therefore, measurement using a standardized open-road course with a clinical CDRS or DRT in the passenger seat of the vehicle will ensure optimal safety of the driver and other road users. Specifically, we will provide state-of-the-art technology (a 2019 Toyota Corolla and a 2020 Toyota Camry, both equipped with instrumentation) for high-impact, low-risk, rigorous measurement of driving to assess users under the influence of medical marijuana and the combined effect of prescription opioid use. As medical marijuana use grows, prescription opioid use continues, and the US population ages, this study provides needed data to develop risk screening, recommendation guidelines, and relevant interventions for this population.

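### One drive 8-12 hours after last use cannot separate lasting effects of long-term marijuana use from residual effects of recent use, yet the article attributes the group difference to the former and describes the drive in conflicting terms

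*Protocol article*

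**What the plan says.** Protocol article, Methods, Study Design (the paragraph after Figure 1): "the estimand of this study is to understand the difference in driving performance errors" between adults with at least a year of daily or near-daily medical marijuana use and matched adults who use none. The paragraph gives a reason for the timing of the drive: "we are intentionally using an 8- to 12-hour timeframe, as that is consistent with how adults in this population report marijuana consumption behavior". It then interprets the contrast, saying that validity is served by "estimating group differences in performance that reflect long-term neuroadaptation and real-world use patterns rather than acute intoxication".

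Assessment Session 2: "For MMG participants only, AS2 will take place 8-12 hours after the last medical marijuana use". Each participant has one drive. Study Design sets the comparator as people with no marijuana exposure for 10 years and no past daily use.

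Discussion, Expected Findings, on the instrumented vehicles used for the same drive: their purpose is "to assess users under the influence of medical marijuana and the combined effect of prescription opioid use".

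Introduction, while calling the evidence mixed: "some studies suggest that impairment due to long-term heavy use does not persist after extended abstinence periods". The Abstract's Conclusions say the data will identify the effects of long-term use and feed risk screening protocols and intervention targets.

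**The concern.** The estimand sentence is a plain group contrast. The interpretation that follows claims more: that the contrast shows long-term adaptation and usual use patterns, and not acute intoxication. The MMG is a group of current users who took the drug within the previous 12 hours. The NMG has neither the long exposure nor the recent one. A worse score in the MMG could come from lasting change, from what remains of recent doses, or from both, and the planned comparison looks the same in each case.

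The distinction matters for the study's stated use. Screening rules and intervention targets built on a lasting effect would differ from those built on an effect of ongoing use that may fade. The Introduction and Abstract also justify the study on the ground that acute effects are known and long-term effects are not, so readers will expect the result to speak to the latter.

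A reader who takes the Expected Findings sentence literally would understand the drive as a test of people currently affected by the drug, which is the state that Study Design says the contrast does not reflect.

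**Working it through.** The article gives no figure for this point, so there is none to reproduce. The check concerns what the contrast identifies.

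**Inputs**
- MMG n = 125, NMG n = 125 (Participants).
- MMG: more than 12 months of near-daily use (Study Design) and last use 8-12 h before the drive (Assessment Session 2).
- NMG: no exposure in 10 years (Study Design).
- One drive per person; no MMG subgroup with a longer interval since use.
- Primary comparison: sum of maneuvers score (SMS), MMG versus NMG, by t test and then ANCOVA (Hypothesis 1a and 1b).

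**Step 1: identification between groups.** Let L be the mean effect on SMS of long-term use that would remain without recent use, and R the added effect of use 8-12 h earlier. Leaving confounding aside:
- NMG mean = μ
- MMG mean = μ + L + R
- Difference = L + R

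A regression with an intercept, an indicator of long-term use and an indicator of use within 8-12 h has identical second and third columns: 1 for the same 125 people, 0 for the other 125. The design matrix has rank 2 with 3 columns. Only L + R can be estimated. No percentage split can be given, and since L and R could have opposite signs, 0% to 100% is not a valid bound either.

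**Step 2: can variation in hours since use within the MMG recover the split?** Assume that times are uniform over 8-12 h, that SMS is in SD units, and that the trend is linear.
- SD of hours since use = 4/√12 = 1.15 h.
- SE of slope = 1/(1.1547 × √125) = 0.077 SD per hour.
- Smallest slope detectable with 80% power at two-sided 5% = (1.960 + 0.842) × 0.0775 = 0.22 SD per hour.
- SE of the MMG mean extrapolated from the window's midpoint (10 h) to 24 h = √(1/125 + (14 × 0.0775)²) = 1.09 SD.
- SE of the MMG-NMG difference as designed = √(2/125) = 0.126 SD.

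The extrapolated mean is 1.09/0.126 ≈ 8.6 times less precise than the planned contrast, at only 24 h and under a linearity assumption that the data could not check. The window carries almost no information on the split.

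**Step 3: the two descriptions side by side.**
- Study Design: the differences "reflect long-term neuroadaptation and real-world use patterns rather than acute intoxication".
- Expected Findings: the vehicles serve "to assess users under the influence of medical marijuana and the combined effect of prescription opioid use".

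The first says that performance is not to be read as acute intoxication; the second says that the drivers are under the drug's influence. Both refer to the same drive, so at least one must change.

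**The case against.** The strongest reply is that the design does what the estimand asks. A reader might infer that the trial cannot deliver its stated estimand. The text does not support that: the estimand is the MMG-NMG difference in driving errors, and neuroadaptation appears only in a later interpretive sentence. That sentence also names real-world use patterns, which can fairly include the usual residue of ongoing use, and it excludes acute intoxication, not every effect of recent use. The window is deliberate and its rationale is given. Participants who fail the field sobriety test do not drive, and the sample size section counts intoxication among reasons for an uncompleted drive. All of this stands.

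A reader might also infer that MMG drivers are still acutely intoxicated at 8-12 hours. Nothing in the article shows how much effect remains then, so this cannot be settled here; nor does the article give any basis for an early-abstinence effect. The Introduction's remark on extended abstinence is one strand of evidence described as mixed. It shows that time since use may matter, but it does not say how this design should separate the components.

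It may also be said that the conflicting phrase in Expected Findings is a single slip in a sentence about vehicles. That is plausible, and it lowers the weight of the contradiction without removing it.

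These replies do not rescue the attribution. The sobriety test classes a participant as failed only when all the nystagmus signs are present, so passing it does not establish that no residual effect exists. Urinary THC-COOH does not fill the gap: Study Design treats it as a measure of chronicity, so adjusting for it could remove the very exposure of interest. The precise assay is reserved for MMG samples, and a group difference cannot be tested within one group.

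**Conclusion.** The concern holds in a limited form. The planned contrast is a legitimate target, but it estimates the combined effect of long-term and recent use; attributing it to long-term neuroadaptation goes beyond what one drive at 8-12 hours can show. The division between the two is unidentified, which does not mean that the residual part is large. The identification result needs no distributional assumption, only that all MMG drivers meet the timing rule and no NMG driver has recent or long-term exposure. The 1.09 SD figure rests on uniform times, linearity and 125 completed MMG drives. Separately, Study Design and Expected Findings conflict on the state of the drivers. Both faults lie in wording, but they bear on what the trial may conclude for screening and intervention guidance, so they should be corrected.

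**What to change.** 1. In Study Design, state the contrast as the SMS difference between habitual users of at least 12 months' standing, under usual use and driving 8-12 hours after last use, and non-users, with any residual effects of recent use included.
2. Delete the attribution to long-term neuroadaptation, or qualify it by saying that the design does not separate lasting from residual effects.
3. Reconcile the Expected Findings description of the drivers with Study Design.
4. In the Abstract's Conclusions, limit the claim to the effect of ongoing habitual use, not a lasting effect.
5. Treat any within-MMG analysis of THC-COOH as exploratory at most, and do not use it as a condition for attributing the group difference to long-term use.

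The timing window, data collection, sample size and primary comparison are unchanged. The cost is a few sentences and a more modest claim. With 30 of 250 participants enrolled as of November 2025, the wording can be settled well before results exist.
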